### Probability, severity, and intensity of adverse drug reactions (ADR)

2.9

All records of commonly occurring ADRs will be maintained throughout the study period. The probability of ADR will be measured using a Naranjo scale,^[24]^ whereas the severity and intensity of ADRs will be evaluated by Hartwig scale and Schumock scale, respectively.^[25]^

### Data handling and record keeping

2.10

All BCM analysis and initial data collection will be performed by the chief investigator himself. Proper patient IDs will be given to each patient to use for future reference throughout the study. Since BP readings and other important clinical parameters will be noted in every dialysis session, a data collection logbook will be used to note pre-, intra-, and postdialysis BP and other information. All data will be collected by the principle investigator. Once in 2 months, all enrolled patients will be visited in HUSM, as per the study protocol. During this visit, patients will undergo routine examinations and routine blood test (complete blood picture) by nephrologists. All data collection forms, incidence reporting forms, and patient logbooks will be kept by the principle investigator and will be used for data analysis. All data will be kept highly confidential to minimize any bias.

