**Method and analysis::**

A single center, prospective, randomized, parallel design, single-blind trial will be conducted in the Malaysian state of Kelantan among postdialysis euvolemic hypertensive patients that are on regular dialysis at least 3 times a week. The primary outcome of the trial will be to note the effectiveness of losartan (RAAS inhibitor) in reducing systolic BP < 140 mm Hg compared to standard non-RAAS-inhibitor antihypertensive therapy. The secondary outcome will be to look at all causes of mortality. A body composition monitor (BCM) will be used to assess postdialysis volume and dry weight. Postdialysis euvolemic patients that have systolic BP > 140 mm Hg will be randomized using Covariate Adaptive Randomization to standard or treatment arm. Participants in the treatment arm will be given 50 mg of losartan once daily except on dialysis days, whereas the standard arm patients will be prescribed non-RAAS antihypertensive agents. The study participants will be followed for a period of 12 months. A Wilcoxon statistical test will be performed to note the difference in BP from baseline up to 12 months using Statistical Package for the Social Sciences (SPSS) 20.

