### Study end point

2.8

A medication dose of 50 mg losartan per day for 3 weeks will be initiated as a test dose to note any incidence of hypotension. If there is no hypotensive event, patients will continue with 50 mg daily every day except dialysis days. The dose could be a titrated dose up to 100 mg/day, depending upon expert opinion and clinical scenario. As for treatment group, the dose titration would be initiated with losartan 50 to 100 mg followed by non-RAAS antihypertensive agents. As for standard group, the choice of dose titration would be left to expert opinion. The primary end point will be achieved by having a postdialysis BP of <140/90 mm Hg and maintaining this for 4 weeks. The secondary end point will be looking at all causes of mortality.

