### Potential risk to subjects

2.11

One of the main potential risks among the study subjects is uncontrolled HTN or hypotension. Patients will be monitored closely to minimize risks. Any patient during the trial with a systolic BP >200 or <110 mm Hg over 3 dialysis sessions will be assessed by the physician in charge, and a decision will be made regarding such patients upon discussion with a panel of experts. Regular blood samples will be taken to avoid any episode of ARB-associated hyperkalemia and other blood abnormalities. Thorough records will be maintained for this purpose. Other minor side effects are common with all antihypertensive medication, including dry cough, nausea, vomiting, dizziness, and headache. Participation in the study is voluntary and all participants will have the right to withdraw from the study. In case of any study-related injury or where a nephrologist feels that the patient might be at risk of study-related injury, the patient will be withdrawn from the study immediately and treated at HUSM. Similarly in case of any ADR developed during the study, the patient will be referred to and treated at HUSM.

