### Statistical analysis

2.13

Results will be expressed as mean or percentage. Comparisons between treatment groups will be made by using a Wilcoxon test after adjustment for the dynamic stratification variables (age, sex, years on dialysis, and diabetes). Cohen d test will be applied to note the effect size. In addition, linear and logistic regression will be applied to note any influence of patient characteristics on treatment outcome. This data will be presented as hazard ratios and 95% confidence intervals. Statistical significance will be set at *P* less than 0.05. All statistical calculations will be performed using Statistical Package for the Social Sciences (SPSS) version 20. Figure 1 provides details of study flow diagram.

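### Blood pressure is logged at every dialysis session, but the stated comparison does not fix which readings form baseline and 12-month BP and names no averaged, serial or baseline-adjusted analysis

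*Protocol article*

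**What the plan says.** Section 2.10 (Data handling and record keeping) states that "BP readings and other important clinical parameters will be noted in every dialysis session", covering pre-, intra- and postdialysis BP. It adds that "patient logbooks will be kept by the principle investigator and will be used for data analysis", without saying how.

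The abstract gives the BP analysis: "A Wilcoxon statistical test will be performed to note the difference in BP from baseline up to 12 months". Section 2.13 (Statistical analysis) gives the between-arm method: "Comparisons between treatment groups will be made by using a Wilcoxon test after adjustment for the dynamic stratification variables". The variables it lists are age, sex, years on dialysis and diabetes. Baseline BP is not among them, and no time point is given. The same section adds that "linear and logistic regression will be applied to note any influence of patient characteristics on treatment outcome". No averaged or repeated-measures analysis is named.

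Serial readings are used elsewhere. Section 2.8 (Study end point) says: "The primary end point will be achieved by having a postdialysis BP of <140/90 mm Hg and maintaining this for 4 weeks". Section 2.11 (Potential risk to subjects) sends for assessment "Any patient during the trial with a systolic BP >200 or <110 mm Hg over 3 dialysis sessions". Section 2.4 (Prescreening) bases entry on 3 consecutive sessions.

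**The concern.** Each patient will have a long series of postdialysis readings, but the continuous comparison is described only as a difference between two ends of follow-up. The article leaves open whether each end is one reading or a mean of several. It also does not use baseline BP as a covariate.

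Two things are at stake.

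- **Precision.** Section 2.12 plans 35 patients per arm before the dropout allowance, and section 3.1 names small sample size as a main limitation. Session-to-session variation within a patient goes straight into a single-reading contrast, and the data needed to reduce it are already being collected. A contrast that requires a 12-month value also has nothing to use from a patient who leaves earlier, unless some rule supplies a value. Section 2.12 anticipates 25% dropout.
- **Freedom of choice.** Section 2.7 blinds only the participants, and section 2.10 has the principal investigator collect all the data. If the defining readings are not fixed in advance, they could be chosen after the results are known.

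**Working it through.** **The plan's own figure.** The 35 per arm in section 2.12 cannot be reproduced. The text shown has no values for the effect, margin, SD or power and does not fix sidedness, possibly because the equation was lost when the file was read. The check therefore works with variance ratios, which do not need those values.

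**Readings available.** Section 2.2 gives 2 to 3 sessions a week, and the abstract gives 12 months of follow-up.

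- Over 12 months: 52 × 2 = 104 to 52 × 3 = 156 postdialysis readings.
- Over 4 weeks: 4 × 2 = 8 to 4 × 3 = 12 readings.

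**Assumptions (not in the documents).** Every reading has the same variance (set to 1), every pair of sessions has the same correlation ρ, and the treatment effect is constant within the averaging window.

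**Step 1: change score, one reading at each end.** Variance = 2(1 − ρ). This is the reference.

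**Step 2: mean of m follow-up readings minus one baseline reading.** Variance = (1 + (m − 1)ρ)/m + 1 − 2ρ = (1 − ρ)(1 + 1/m). Relative to step 1 this is (1 + 1/m)/2, so ρ cancels.

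| m | Ratio |
|---|---|
| 6 | 0.58 |
| 8 | 0.56 |
| 12 | 0.54 |
| 104 | 0.505 |
| 156 | 0.503 |

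Nearly all the gain comes from the first 6 to 12 readings. Using the full year adds little.

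**Step 3: 3 baseline readings averaged as well.** The ratio is (1/3 + 1/m)/2.

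- m = 8: (0.333 + 0.125)/2 = 0.23.
- m = 12: (0.333 + 0.083)/2 = 0.21.

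**Step 4: adjusting for baseline BP.** With one reading at each end, the ANCOVA residual variance is 1 − ρ². Relative to step 1 this is (1 + ρ)/2, which is 0.65 at ρ = 0.3 and 0.90 at ρ = 0.8. With a 3-session baseline and a 12-reading follow-up mean, the residual variance is (1 + 11ρ)/12 − ρ²/[(1 + 2ρ)/3].

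- ρ = 0.3: 0.358 − 0.09/0.533 = 0.190. Divided by 1.4, this is 0.14.
- ρ = 0.8: 0.817 − 0.64/0.867 = 0.078. Divided by 0.4, this is 0.20.

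So ANCOVA on the means does somewhat better than the change score of step 3. Averaging and baseline adjustment are separate gains.

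**Step 5: sensitivity to the equal-correlation assumption.** Suppose sessions within the same window correlate at 0.7 and sessions from different windows at 0.5. The single-reading change variance is 2(1 − 0.5) = 1.0.

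- 12 follow-up readings, one baseline reading: (1 + 11 × 0.7)/12 + 1 − 2 × 0.5 = 0.725, a ratio of 0.73 instead of 0.54.
- 3 baseline readings averaged as well: 0.725 + (1 + 2 × 0.7)/3 − 1 = 0.525, a ratio of 0.53 instead of 0.21.

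The gain shrinks but does not vanish.

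**The case against.** The strongest reply is that the article never describes a single-reading contrast. The abstract's wording on the BP difference does not tie the far end to one reading, and section 2.13 names no time point. The primary end point in section 2.8 needs 4 weeks of readings, the safety rule in section 2.11 uses 3 sessions, and section 2.10 puts the logbooks to use in analysis. A reader might infer that most of the collected readings are thrown away. The documents do not say so, and these sections point the other way. The loss is therefore conditional on one reading being used at each end.

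It can also be said that the choice of readings is commonly left to an analysis plan, which is not shown. That is fair for the detail, and silence alone would not be a finding. But the article does name its method, in both the abstract and section 2.13: a Wilcoxon test, with a list of adjustment variables that omits baseline BP. A more precise method using data already recorded is available, so the point goes beyond missing detail.

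A third reply is that averaging changes what is estimated. That would hold for a mean over the whole year, which would include the titration period. A mean over the last 4 weeks keeps the 12-month target.

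Finally, a reader might turn the variance ratios into a power gain or a saving in patients. The documents do not support this. Section 2.12 as shown gives no SD, effect, power or fixed sidedness, and if the planning SD already reflected averaged BP there would be no gain over the planned power. Nor should the variance of the follow-up mean alone, (1 + (m − 1)ρ)/m, be taken as the gain, because the stated contrast is a difference from baseline.

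**Conclusion.** The point stands as a conditional one about efficiency and specification. The plan collects BP at every session, names only a Wilcoxon comparison of the baseline to 12-month difference, does not fix the readings behind either value, and does not adjust for baseline BP.

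If single readings are used, averaging the last 4 weeks alone nearly halves the change-score variance, and averaging 3 baseline sessions too brings it to a little over a fifth. Both figures rest on equal correlation between sessions and a constant effect within the window. Higher correlation between nearby sessions weakens them, as step 5 of the working shows. If the investigators already intend to average, what remains is to say so and to add the baseline adjustment.

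The change should be made, but the plan is not invalid without it. A 12-month contrast is a legitimate target.

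**What to change.** For the continuous BP comparison:

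- Define baseline as the mean postdialysis BP over 3 consecutive pre-treatment sessions.
- Define 12-month BP as the mean of all postdialysis readings in the last 4 weeks of follow-up.
- Compare arms by ANCOVA, with baseline BP and the minimisation factors (age, sex, diabetes, years on dialysis) as covariates.
- Add a mixed model on monthly means as the supporting analysis, so that patients who leave early contribute the readings they have.
- State how this comparison relates to the end point of section 2.8, sustained control for 4 weeks. The abstract describes the primary outcome as "effectiveness of losartan (RAAS inhibitor) in reducing systolic BP < 140 mm Hg", with no 4-week condition, so the relation needs to be explicit.

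The cost is analysis wording and data entry from the logbooks. No extra visits or measurements are needed, because the readings are already recorded.

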### Trial design

2.1

The current study will be a single-center, prospective, randomized, parallel-design, single-blind trial that would be conducted in the Malaysian state of Kelantan at a CKD resource center of the Hospital Universiti Sains Malaysia (HUSM) and its associated dialysis centers. The study protocols are approved by the Ethical and Research Committee of Universiti Sains Malaysia (USM/JEPeM/15050173), and the trial is registered under Australia New Zealand Clinical Trial Registry (ACTRN12615001322527). The study purpose will be explained, and patients’ consent will be obtained before enrolling by the principle investigator.

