### Standard and intervention arms

2.7

Both the standard and intervention arms will be randomized with equal numbers of patients. The standard-arm patients will receive antihypertensive therapy except RAAS inhibitors that included calcium-channel blockers, diuretics, alpha- and beta-blockers, whereas the intervention-arm patients will be prescribed ARB (losartan) alone or in combination with standard antihypertensive pharmacotherapy. In both study arms, patients will be allowed multiple antihypertensive pharmacotherapies to control BP, after discussion with a panel of experts. However, this will only be done where entirely necessary to avoid any deterioration to a patient's health. Finally, study intervention (losartan) and antihypertensive medication will be given to the patients on a weekly basis by the principle investigator. A member of patient's family will be consented to monitor a patient's adherence at home whereas a pill check will be performed once a week. Only the study participants will be blinded during the course of study.

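### The investigator who dispenses treatment, and so knows the arm, also collects the blood pressure data behind the primary end point, and the stated safeguard does not cover that step

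*Protocol article*

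**What the plan says.** Section 2.1 of the protocol article describes a "randomized, parallel-design, single-blind trial". Section 2.7 says who is covered: "Only the study participants will be blinded during the course of study". The same section states that "study intervention (losartan) and antihypertensive medication will be given to the patients on a weekly basis by the principle investigator".

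Section 2.10 sets out data collection. Blood pressure is noted at every dialysis session, and "a data collection logbook will be used to note pre-, intra-, and postdialysis BP and other information". It continues: "All data will be collected by the principle investigator". On custody, it says "All data collection forms, incidence reporting forms, and patient logbooks will be kept by the principle investigator and will be used for data analysis". It closes by offering confidentiality of the data as the measure against bias.

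Section 2.8 defines the primary end point as a postdialysis blood pressure below 140/90 mm Hg, maintained for 4 weeks.

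**The concern.** Participant blinding protects against changes in patients' behaviour. It does nothing for the step at which a blood pressure value enters the record. Here that step belongs to a role that knows the allocation. The outcome is also a cut-off, so small choices about which reading is logged, when it is taken or how it is rounded can change a patient's status.

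If such choices differed between arms, they could produce an apparent treatment difference with no drug effect, or hide a real one. Both uses of the outcome are exposed, because the threshold end point and the comparison of blood pressure over 12 months described in the abstract would draw on the blood pressure data collected under section 2.10. All-cause mortality, the secondary outcome, is little exposed.

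**Working it through.** The point turns on the stated roles, so the first check is to set the sections side by side.

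1. **Knowledge of arm.** Section 2.7 limits blinding to participants and gives weekly dispensing of losartan and the other drugs to the principal investigator. That role therefore knows who receives losartan.
2. **Collection of the outcome.** Section 2.10 gives all data collection to the same role and lists postdialysis blood pressure among the logbook entries.
3. **Custody.** Section 2.10 leaves forms and logbooks with the same role up to analysis.
4. **Dependence of the end point.** Section 2.8 builds the primary end point on postdialysis blood pressure, which is among those entries.
5. **Safeguards.** Confidentiality (section 2.10) keeps data from outsiders, not from the collector. Computer randomization (section 2.5) protects assignment, not measurement. The limitations (section 3.1) discuss the lack of consensus on how to measure blood pressure in these patients but not observer bias.

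Steps 1 to 4 hold from explicit statements. Step 5 shows that no stated measure covers the gap.

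**Size, as an illustration only.** The plan has no figure to reproduce here.

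Inputs:
- n = 35 per arm, from section 2.12.
- Alpha 0.05, from section 2.13. Sidedness is not stated there; two-sided is assumed.
- SD of systolic pressure and differential recording shift b: both assumed, neither in the documents.
- Power of 80%: assumed, and used only for the detectable difference.
- A normal approximation for a difference in means stands in for the planned Wilcoxon test.

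Type I error with no true effect:
- SE = SD × √(2/n) = 15 × √(2/35) = 3.59 mm Hg.
- b/SE = 3/3.59 = 0.84.
- Type I error = [1 − Φ(1.96 − 0.84)] + Φ(−1.96 − 0.84) ≈ 0.131 + 0.003 ≈ 0.13, against a nominal 0.05.

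Range over other assumptions, 35 per arm:

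| SD (mm Hg) | shift 2 | shift 3 | shift 5 |
|---|---|---|---|
| 10 | 0.133 | 0.241 | 0.552 |
| 15 | 0.086 | 0.133 | 0.286 |
| 20 | 0.070 | 0.096 | 0.182 |

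With 44 per arm (the total after the dropout allowance), the range is 0.076 to 0.65.

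For scale, the difference detectable with 80% power is (1.96 + 0.84) × √(2/35) = 0.67 SD, or about 10 mm Hg at SD 15. A 3 mm Hg shift is about 0.3 of that (3/10).

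**The case against.** The strongest reply is that collecting data need not mean taking the measurement. Section 2.10 does not say who operates the cuff or whether the device is automatic. If others take the readings and the investigator only transcribes them, there is less room for influence. That stands, and it limits the claim: the text supports collection and custody by an unblinded role, not personal measurement. Selection and transcription would still be exposed.

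The sustained end point also blunts the effect of any single reading. At the 2 to 3 sessions a week in section 2.2, 4 weeks means 8 to 12 sessions (2 × 4 to 3 × 4). A calculation for one reading near 140 mm Hg would therefore not describe the stated end point, and none is used here.

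Several stronger readings are tempting but not supported:
- **That single-blind is the wrong label.** Section 2.7 says exactly who is blinded, so the term is used correctly.
- **That participant blinding must fail**, because losartan is generally omitted on dialysis days and no placebo is described. Both arms may take several drugs, and how blinding is carried out is detail an article may leave to the full protocol.
- **That the principal investigator also checks the pills.** Section 2.7 names nobody for that check.
- **That independent unit readings already exist.** Section 2.10 describes the trial's own logbook and mentions no unit charts or automatic monitor.
- **That the volume assessments are exposed in the same way.** Section 2.10 says "All BCM analysis and initial data collection will be performed by the chief investigator himself", but does not say whether this is the same person as the principal investigator.

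Brevity of the article is not an answer to the core point. The restriction of blinding to participants is a positive statement, so a blinded assessor cannot be assumed to stand in a fuller document.

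**Conclusion.** The concern holds in a limited form. By the protocol's own statements, one unblinded role dispenses treatment, collects the primary outcome data and keeps the records used for analysis, and confidentiality does not address observer or selection bias. This should be corrected.

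A reader might infer that the primary result will be biased, or by how much. The documents support neither. The rise in type I error to about 0.13 assumes SD 15, a 3 mm Hg differential shift and two-sided alpha; the comparison with the detectable difference also assumes 80% power. The shift is hypothetical, and the calculation concerns mean systolic pressure, not the proportion meeting the 4-week end point. It shows only that a modest differential shift would matter in a trial of this size.

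**What to change.** In section 2.10, state that:
- the outcome blood pressure is the reading noted at every dialysis session at one fixed post-session time; 30 minutes is already used at screening in section 2.4;
- all such readings in the assessment window count, with no selection or replacement by the dispensing investigator;
- where existing unit staff or devices already record blood pressure, which the sponsor should confirm, those stored readings are the source;
- the end point is classified and the analysis run on masked arm codes.

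In section 3.1, acknowledge unblinded outcome collection as a limitation. Using unit readings would separate recording from dispensing but would not by itself make it blind, since section 2.7 blinds participants only; hence the all-readings rule and the masked classification.

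The cost is wording and a little data-handling work. Treatment and sample size do not change.

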### Potential risk to subjects

2.11

One of the main potential risks among the study subjects is uncontrolled HTN or hypotension. Patients will be monitored closely to minimize risks. Any patient during the trial with a systolic BP >200 or <110 mm Hg over 3 dialysis sessions will be assessed by the physician in charge, and a decision will be made regarding such patients upon discussion with a panel of experts. Regular blood samples will be taken to avoid any episode of ARB-associated hyperkalemia and other blood abnormalities. Thorough records will be maintained for this purpose. Other minor side effects are common with all antihypertensive medication, including dry cough, nausea, vomiting, dizziness, and headache. Participation in the study is voluntary and all participants will have the right to withdraw from the study. In case of any study-related injury or where a nephrologist feels that the patient might be at risk of study-related injury, the patient will be withdrawn from the study immediately and treated at HUSM. Similarly in case of any ADR developed during the study, the patient will be referred to and treated at HUSM.

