### Sample size

2.12

The sample size for the current study was based on a statistical superiority trial (continuous data) design of a randomized control trial. To verify that a new treatment is more effective than a standard treatment from a statistical point of view or from a clinical point of view, its corresponding null hypothesis is that the new treatment is not more efficacious than the control treatment by a statistically/clinically relevant amount. Based on the nature of the relevant amount, a superiority design contains statistical superiority trials and clinical superiority trials.^[26]^

Where N is the size per group, *p* the response rate of standard treatment group; *p* 0 the response rate of new drug treatment group; *z* the standard normal deviate for a 1 or 2 sided *x*; *d* the real difference between 2 treatment effect; a clinically acceptable margin; and S is the Polled standard deviation of both comparison groups. 

Calculating the sample size using the equation above: 

N = 35

The sample size calculated from statistical superiority for randomized control trial is 35 for each arm of the treatment, so altogether 70 euvolemic hypertensive patients should be recruited for the current study. Since a 25% dropout rate has to be anticipated, the final total was 88:44 in each arm.

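### Section 2.11 takes injured or at-risk patients out of the study itself, with no follow-up stated, so blood pressure and mortality data can be lost for treatment-related reasons

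*Protocol article*

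**What the plan says.** Potential risk to subjects (2.11) sets out three situations and treats them differently.

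- **Injury or risk of injury.** After a study-related injury, or "where a nephrologist feels that the patient might be at risk of study-related injury", the rule is that "the patient will be withdrawn from the study immediately and treated at HUSM".
- **Adverse drug reactions.** "in case of any ADR developed during the study, the patient will be referred to and treated at HUSM". Withdrawal is not mentioned.
- **Systolic pressure above 200 or below 110 mm Hg over three sessions.** The physician assesses the patient and "a decision will be made regarding such patients upon discussion with a panel of experts". Again, removal is not mentioned.

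On blinding, Standard and intervention arms (2.7) says: "Only the study participants will be blinded during the course of study".

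Study end point (2.8) defines the primary end point as postdialysis pressure below 140/90 mm Hg held for 4 weeks, and the secondary as death from any cause. The abstract gives 12 months of follow-up. Section 2.8 also describes a losartan run-in: "A medication dose of 50 mg losartan per day for 3 weeks will be initiated as a test dose to note any incidence of hypotension". It then says: "If there is no hypotensive event, patients will continue with 50 mg daily every day except dialysis days". It does not say what happens to patients who do have an event.

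Sample size (2.12) requires 35 per arm and raises this to 44: "Since a 25% dropout rate has to be anticipated". Data handling and record keeping (2.10) has blood pressure logged at each dialysis session.

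**The concern.** Stopping a drug and leaving a trial are different events. Section 2.11 merges them: once the injury rule applies, the patient leaves the study, and nothing provides for further readings or a check of vital status.

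Three features make this loss likely to be informative.

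- **The trigger can depend on treatment.** Hypotension, uncontrolled hypertension and ARB-associated hyperkalemia are the hazards named in 2.11, and the last belongs to the losartan arm.
- **The trigger is partly a matter of judgement.** The clinician who judges knows the allocation, so opinions about losartan can affect who leaves.
- **Those who leave are those judged most at risk.** Their later deaths and pressures matter most to the two end points.

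A patient withdrawn before completing 4 weeks at target has an undetermined primary outcome, and a death after withdrawal may go uncounted. An analysis plan can define analysis sets and missing-data methods, but it cannot recover observations that were never made.

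**Working it through.** **1. Which passages remove patients.** Of the three situations in 2.11, only injury or judged risk of injury leads to stated withdrawal from the study. Adverse drug reactions go to referral, and extreme pressures go to an expert panel. The test-dose text in 2.8 describes who continues the dose and is silent on the rest. The point therefore rests on the injury rule.

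**2. The plan's own figure.** Inputs from 2.12 are 35 per arm and 25% dropout.

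- 35 × (1 + 0.25) = 43.75, rounded up to 44 per arm, 88 in total. This reproduces the stated figure.
- The base of 35 cannot be reproduced, because the text gives no values for power, difference, SD or margin.

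**3. What remains if the whole allowance is lost.** This is an illustration, since 2.12 does not attribute the 25% to the injury rule.

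- Lost: 0.25 × 44 = 11 per arm. Remaining: 44 − 11 = 33 per arm, 66 in total. This is below the required 35.
- Assume 80% power at two-sided 5%. Then 35 per arm detects (1.960 + 0.842) × √(2/35) = 0.67 SD.
- Power for that difference, Φ(0.67 × √(n/2) − 1.960), is about 78% with 33 per arm, 80% with 35 and 88% with 44. The 88% assumes that readings off study drug do not dilute the effect.

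**4. Direction of bias.** Assume a true response of 50% and that 10% of one arm is lost.

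- All lost patients responders: (0.50 − 0.10)/0.90 = 44.4%.
- All lost patients non-responders: 0.50/0.90 = 55.6%.

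The same amount of loss can make an arm look worse or better, depending on why patients leave. The document does not say which will dominate.

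**5. Deaths.** The document gives no mortality rate, so assume 5% to 20% over 12 months.

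- Expected deaths among 88: 88 × 0.05 = 4.4 to 88 × 0.20 = 17.6.
- If 22 patients (25% of 88) left at mid-trial, about half their follow-up would be lost. Deaths missed at average risk: 22 × 0.05/2 = 0.55 to 22 × 0.20/2 = 2.2.
- At double risk: 1.1 to 4.4.

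With so few events expected, one or two missed deaths in one arm would matter.

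**6. Whether the data are within reach.** Section 2.10 records pressure at each dialysis session, 2.1 places the trial at the hospital and its associated dialysis centers, and 2.11 sends the withdrawn patient to the same hospital. Collection looks feasible for anyone still dialysing there. The document does not say that recording continues after withdrawal.

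**The case against.** The strongest objection is that this is a condensed article. It does not say that observation ends at withdrawal, it has the patient treated at the trial hospital, and the abstract promises 12 months of follow-up. Analysis sets and missing-data handling may sit in documents not shown. This stands to the extent that the loss is a risk and not a demonstrated fact. It does not remove the point, because the article states a rule, and followed as written that rule ends participation.

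Three stronger readings are tempting, and the text does not support them.

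- **The test dose screens losartan patients out.** A reader might infer this from 2.8. The sentence concerns continuing a dose, not staying in the study, and 2.11 gives a route for low pressure without removal. Even the timing of the test dose after randomisation is only likely, since the flow diagram is not shown.
- **A completers analysis is planned.** A reader might infer this from the dropout inflation. Inflating for dropout is routine whatever the analysis set, and nothing excludes withdrawn patients from the analysis.
- **Losartan's effect is biased by a known amount, in a known direction.** The document gives no withdrawal rate by arm and no SD, and the injury rule applies to both arms. Any such figure would reflect only what was assumed about who leaves.

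One further caution stands: the remedy must not turn a mandatory safety action into a discretionary one.

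**Conclusion.** The point holds for the injury rule in 2.11. It removes patients from the study, on the judgement of an unblinded clinician and for reasons that can depend on treatment, with no stated follow-up. Both end points are exposed to informative loss. The size and direction are unknown. The fall to 33 per arm is an illustration that assumes the entire 25% allowance is lost; the power figures further assume 80% power at two-sided 5% for the original 35. The death counts rest on assumed mortality. On the test dose, the finding is only that the article does not say what happens to patients with a hypotensive event. This should be changed: in a trial of 88, the data at risk appear cheap to collect and could not be recovered later.

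**What to change.** Leave the clinical trigger and the clinical action in 2.11 exactly as they stand, and add a sentence on data collection such as:

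*Withdrawal under this section does not end data collection. Unless the patient withdraws consent, blood pressure from routine dialysis sessions and vital status will be recorded to month 12 for every randomised patient.*

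In Statistical analysis (2.13), add that every randomised patient is analysed in the assigned arm, including any with a hypotensive event during the losartan test dose. Section 2.8 should also say how such patients are followed for data; their clinical care is for the investigators to settle.

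The cost is a protocol and consent amendment. The abstract dates the first enrolment to 10/12/2015 and the formal start to 16/02/2016, so enrolled patients may need to consent again. Readings taken off study drug will dilute the treatment effect somewhat. Extra data work should be small where patients still dialyse at the participating centers, since pressures are already logged at each session.
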